### Hypotheses

We hypothesise that Snow Control participants in the therapy group will show higher reductions on the Severity of Dependence Scale (SDS) [20] sum score and cocaine consumption than those in the control group at the 6-week treatment termination and at the 6-month follow up. Moreover, we expect participants in the therapy group to improve more significantly with respect to the secondary outcomes between baseline and 6-week treatment termination. We also expect the participants in the therapy group to show significantly higher retention.

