### Estimation of the Expected Effect Sizes and Sample Size

The maximal SDS score is 15 points, and the average SDS standard deviation in previous studies was 5 points. As we expect relatively large cocaine consumption differences between participants, we expect a conservative SDS deviation of 7.5 points. For a successful reduction in cocaine use, an average 25% SDS score reduction (3.75 points reduction for a small to medium effect size) is anticipated. This results in a total sample of 25 participants in each group (α = .05, 1-β = 0.8). According to the pilot study, we expect 70% of the participants to quit the study before completion at six weeks. We thus aim to recruit a total of 170 participants at baseline.

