During the online implementation of the consumption diary of the Snow Control therapy group, we considered asking pilot participants to note the number of cocaine lines consumed. The pilot tests showed that although this includes some numeracy skills, pilot participants did not feel disturbed to note their consumption in grams of cocaine consumed per day. However, because the well-established SDS is utilised as the main outcome and the CCQ-B as a secondary instrument with a randomised control group, we do not expect much influence of purity and quality of the cocaine consumed or the methods of consumption to interfere with the potential outcome differences.

Finally, a potential problem for this trial is the expected high number of lost participants at the end of and at follow up of the online therapy, which will likely be even higher in the control intervention. We will address this issue in three ways. 1) All participants must invest approximately 30 minutes for the baseline assessment, which will select rather motivated participants and prevent the participation of un-motivated participants. 2) Participation at 6 months follow up assessment will be compensated by a 40 Euro incentive (an online voucher or an online charitable donation). 3) All missing values in the final data set will be multiple-imputed, a promising approach that, as shown by our Dutch colleagues, has become increasingly important in e-health research [34].

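### The recruitment target of 170 allows for loss only up to six weeks, while the primary SDS hypothesis also applies at 6 months, so the stated 25 per group and 80% power make no allowance for later loss

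*Protocol article*

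**What the plan says.** All references are to the protocol article.

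- **Estimation of the Expected Effect Sizes and Sample Size.** The inputs are a past SD ("the average SDS standard deviation in previous studies was 5 points"), a larger SD for sizing ("we expect a conservative SDS deviation of 7.5 points") and a target effect ("an average 25% SDS score reduction (3.75 points reduction for a small to medium effect size) is anticipated"). The result is "This results in a total sample of 25 participants in each group (α = .05, 1-β = 0.8"). The only attrition allowance follows: "we expect 70% of the participants to quit the study before completion at six weeks". From this comes the recruitment target of 170.
- **Aims of the trial.** The primary outcome is change in SDS across baseline, 3 weeks, 6 weeks and the 6-month follow-up. Table 2 schedules the SDS at all four.
- **Hypotheses.** The therapy group is expected to reduce SDS score and cocaine consumption more "than those in the control group at the 6-week treatment termination and at the 6-month follow up". The next sentence places the secondary outcomes between baseline and week 6 only.
- **Discussion.** The authors name as a potential problem "the expected high number of lost participants at the end of and at follow up of the online therapy". Their answers are a long baseline assessment that selects motivated participants, a 40 Euro incentive at 6 months, and multiple imputation. No 6-month loss rate is given.
- **Data Analysis.** The repeated measures ANOVA is described for three and six weeks.

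**The concern.** The plan makes a primary claim at two time points, expects loss at both, and allows for loss at only one. The inflation leaves a margin of one participant at week 6, so a net further loss of two takes the total below 50. The power statement itself carries no time point.

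A non-significant SDS difference at 6 months could then be read as evidence against a lasting effect, on the belief that the comparison had 80% power. The sizing does not support that belief.

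**Working it through.** **Inputs.** From the sample-size section: 25 per group, 80% power, α = 0.05 (sidedness not stated; two-sided used here), difference 3.75, SD 7.5 (or 5 from earlier studies), 70% loss by six weeks, 170 recruited. The later loss is not in the document, so I assume a net 10%, 20%, 30% or 40% of the six-week completers. Net means after counting any early dropouts who return.

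**Step 1: the plan's inflation.** N = 2 × 25 / (1 − 0.70) = 50 / 0.30 = 166.7, stated as 170. This reproduces. Expected completers at week 6: 170 × 0.30 = 51, or 25.5 per group.

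**Step 2: the loss that 170 can absorb.** 50 participants remain if total loss is at most 1 − 50/170 = 0.706. The six-week allowance already takes 0.70 of this.

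**Step 3: numbers at 6 months.** Number remaining = 51 × (1 − further loss). Total loss = 1 − 0.30 × (1 − further loss).

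**Step 4: power at 6 months** (two-sample t-test, two-sided). Two effect sizes are used so that this fault is kept apart from the one in the base calculation.

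- *Plan's premise*: solve for the d at which 25 per group gives 80%. This is d ≈ 0.81.
- *Stated inputs*: d = 3.75 / 7.5 = 0.50.

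| Net loss after week 6 | Total loss | Remaining (per group) | Power, plan's premise (d ≈ 0.81) | Power, stated inputs (d = 0.50) |
|---|---|---|---|---|
| 0% | 70% | 51 (25.5) | 0.81 | 0.42 |
| 10% | 73% | 46 (23.0) | 0.76 | 0.38 |
| 20% | 76% | 41 (20.4) | 0.71 | 0.34 |
| 30% | 79% | 36 (17.9) | 0.65 | 0.31 |
| 40% | 82% | 31 (15.3) | 0.58 | 0.27 |

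With SD 5 (d = 3.75 / 5 = 0.75), power is 0.75 with no further loss and 0.70, 0.65, 0.59 and 0.52 down the rows. One-sided at SD 5, a 10% loss just reaches 0.80 and 20% does not.

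**Step 5: what belongs to this point.** The first row has no later loss, yet the stated inputs give only 0.42. The drop from 0.80 to 0.42 therefore arises in the base calculation: a two-sided comparison of two groups at d = 0.50 needs about 63 per group by the normal approximation, not 25. Only the movement down each column is due to later loss.

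**Step 6: precision at 6 months.** The 95% confidence-interval half-width is t(0.975, 2n − 2) × SD × √(2/n). With SD 7.5 it is about 4.2 points at n = 25.5 per group and 4.5, 4.7, 5.1 and 5.5 points at the four assumed losses. All of these exceed the 3.75-point target.

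**The case against.** Several counter-arguments have weight.

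- **Early dropouts may return.** Under Trial Flow, follow-up is timed from baseline alone, the 6-month invitation goes to participants by e-mail, and the 40 Euro payment is tied to that assessment. If 20% of completers were lost, 41 would remain, and about 9 of the 119 early dropouts (170 − 51), or 8%, would restore 50. A reader might infer that the 6-month comparison is certain to fall below 25 per group. The document does not establish that. It does not quantify any return either, its section on dropouts treats non-responders as having left the study, and the Discussion still expects high loss at follow-up. The shortfall is therefore conditional.
- **The low power is mostly another fault.** This is correct for the d = 0.50 figures. A reader might attribute the whole distance from 0.80 to 0.27 to follow-up loss. The zero-loss row shows that this would be wrong. The column on the plan's own premise shows what remains: modest at 10% to 20%, larger beyond that.
- **The sizing already reads as six-week sizing.** The attrition sentence names six weeks, and the ANOVA names three and six. That is a fair reading, but it leaves the 6-month primary hypothesis with no sizing at all, and the document does not say so.
- **Multiple imputation keeps everyone in the analysis.** It does, but it does not restore unobserved SDS information. The plan itself inflates for six-week loss despite intending to impute.
- **No arithmetic error is shown in the inflation.** True: 50/0.30 is correctly worked. The fault lies in what the figure covers.

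**Conclusion.** The point holds in a limited form. The stated 25 per group and 80% power make no allowance for loss after week 6, although the primary SDS hypothesis extends to 6 months and loss is expected there. The figures carry over to 6 months only if total loss stays at or below about 70.6%.

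On the plan's own premise, an assumed net further loss of 10% to 40% lowers power from 0.81 to between 0.76 and 0.58. On the stated difference and SD it falls from 0.42 to between 0.38 and 0.27. These results rest on assumed loss rates, equal groups and a two-sided two-sample t-test. The failure of the stated inputs to give 80% even at six weeks is a separate and larger matter, and it should be settled first.

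**What to change.** Keep the recruitment target of 170 and amend the sample-size section in this order:

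1. Recompute the power of 25 per group from the stated SD and difference, giving the test and its sidedness. Tying the present 80% to week 6 without this step would reaffirm a figure that the stated inputs do not support.
2. State that the sizing and the 70% loss refer to six weeks.
3. State an assumed total loss at 6 months, the number then expected to have an SDS score, and the resulting power or confidence-interval half-width.
4. Do not apply the 80% to 6 months, and say that a null 6-month result will be interpreted by its confidence interval.

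The 6-month hypothesis need not be relabelled as secondary. That would change the outcome hierarchy and is a separate decision. The cost is a few sentences and a less favourable stated figure, with no extra recruitment.

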### Consent Procedure

The rationale of the study will be explained to the participants. They will also be informed about the different assessments, assessment schedules and duration. The participants will then be informed about (1) study inclusion and exclusion criteria (see table 1), (2) the potential risks of participation, (3) safety arrangements during and after the study phase, (4) the inability of Snow Control to replace face-to-face therapy for problematic cocaine use/abuse, and (5) the circumstances under which they should contact their general practitioner or a professional from the medical advisory and emergency list that will be accessible at all times and how to make this contact. The participants will also be informed that the study has been reviewed by the ethic committee of the Canton of Zurich and given their declaration of no objection (nihil obstat). Moreover, they will be informed about their right to withdraw from the study at any time without consequences except for the loss of further compensation. Informed consent will be accepted when participants click on a field on the informed consent page and submit the consent with a submission button.

**Table 1 T1:** Inclusion and exclusion criteria and reasoning

*Inclusion Criteria*	Reasoning
- Minimal age of 18 years	To ensure a minimal age of participation
- Cocaine use > 2 occasions in the last 30 days	To include occasional users in order to provide extended study validity
***Exclusion Criteria***	**Reasoning**
- Participation in other psycho-social or pharmacological treatments for the reduction/cessation of cocaine use	To avoid confounding of treatment effects
- Opioid use in the last 30 days (exception: substitution maintenance treatment for opioid dependence without heroin use in the last 30 days)	To avoid confounding of drug effects
- Ever been in treatment for cardiovascular problems or apoplexy	To avoid subjects with these problems entering the study
- BDI-V score > 45	To avoid subjects with serious symptoms of depression entering the study

### Baseline Assessment

After providing informed consent, subjects who meet study entry criteria will create a personal and secure login and password (with automated real-time verification of the passwords' security level) and will receive an automated e-mail notification with their access information. They will then be directed to the baseline assessment on socio-demographic characteristics and consumption patterns (see table 2). Participants that do not meet the inclusion and/or meet one of the exclusion criteria (see table 1) will receive an explanation about why they are not permitted to participate in the study and be provided recommendations (e.g., not to reduce their consumption of cocaine before visiting a physician to receive more accurate treatment, etc.). A corresponding decision tree for the possible inclusion and exclusion criteria combinations will be constructed and implemented. The completion of the baseline assessment will allow participants to begin the Snow Control therapy or the control tool according to an automated online allocation procedure. Participants that do not fulfil the criteria can proceed with the Snow Control therapy modules, though without study participation (no assessments and no compensation).

**Table 2 T2:** Measurements and instruments

Assessments/instruments	Baseline	3 weeks	6 weeks	6-month follow up
Socio-demographics	x			
Previous psychiatric and somatic treatments	x			
SDS	x	x	x	x
CCQ-B	x	x	x	x
FDA	x	x	x	x
BDI-V	x		x	x

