### Randomisation and Allocation

Once participants have completed their baseline assessment, they will be randomly brought to part 1 of either the intervention or the control tool, and this assignment will be automatically registered in the background database. This assignment will also be registered in their Internet browser as a cookie to avoid multiple registrations by one person. If a person returns to the Snow Control start page and attempts to register for a second time, she or he will be recognised by the background database and automatically be redirected to his or her allocation.

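### As described, people who have already used the Snow Control modules, after failing screening or in the pilot, can later be randomised, because prior Snow Control use is not an exclusion

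*Protocol article*

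**What the plan says.** Four statements in the protocol article bear on this point.

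- **Handling of screening failures (Baseline Assessment).** People who do not meet the criteria "will receive an explanation about why they are not permitted to participate in the study". The same section then says: "Participants that do not fulfil the criteria can proceed with the Snow Control therapy modules, though without study participation". They have no study assessments and receive no compensation.
- **Exclusions (Consent Procedure, Table 1).** The only treatment-related exclusion is "Participation in other psycho-social or pharmacological treatments for the reduction/cessation of cocaine use". Its stated reason is to prevent confounding of treatment effects. Earlier use of Snow Control is not named there or anywhere else.
- **Duplicate check (Randomisation and Allocation).** The sequence is: "Once participants have completed their baseline assessment, they will be randomly brought to part 1 of either the intervention or the control tool". The assignment goes into the background database, and "This assignment will also be registered in their Internet browser as a cookie to avoid multiple registrations by one person". A returning person is sent back to the arm already allocated.
- **Logins (Baseline Assessment).** Account creation is described for people who pass: "subjects who meet study entry criteria will create a personal and secure login and password". How ineligible users get into the modules is not described.

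A pilot took place: the sample size section takes its dropout rate from it, and the Discussion reports pilot participants' views on the consumption diary. Recruitment runs partly through the Snow Control website (Study population).

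**The concern.** The trial compares Snow Control with psycho-education, so it needs people who have not already had Snow Control. The article gives the experimental therapy to people it turns away, and its eligibility list has no line that keeps them out if they come back.

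Such a person may enter with part of any benefit already in the baseline SDS score. In the control arm, that person is no longer a psycho-education-only comparison. In the therapy arm, that person repeats material already seen. Both tend to bring the arms together. This works against the article's own reason for its treatment exclusion.

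**Working it through.** The plan states no figure on this point, so the check is mainly a reading of the passages side by side.

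**Step 1: can a person who failed screening have used the therapy?** Yes. Baseline Assessment allows it explicitly. Pilot participants are a second possible source.

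**Step 2: can that person become eligible later without misreporting?** Table 1 has six criteria. Five can change with time: reaching age 18, cocaine use in the last 30 days, participation in other treatment (read as current participation), opioid use in the last 30 days, and BDI-V score. Only the cardiovascular/apoplexy criterion is worded as ever, so it cannot lapse.

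**Step 3: does Table 1 stop them?** Not as worded. Read naturally, other treatments means treatments other than Snow Control. Table 2 records previous psychiatric and somatic treatments at baseline, but it does not name Snow Control and is not an eligibility rule.

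**Step 4: does the duplicate check stop them?** Not as described. The cookie stores the assignment, and the database redirects to an allocation. Assignment follows completion of the baseline assessment, so a person who failed screening has none. Someone excluded on BDI-V might already hold a login, because BDI-V is also listed as a baseline instrument, but the redirect would still need an allocation.

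**Step 5: what would it do to the contrast?** Inputs: 3.75 SDS points and a recruitment target of 170, both from the sample size section. Assumptions:
- 3.75 is taken as the between-arm difference; the article words it as an average reduction.
- A share q of those randomised has prior exposure, equal in the two arms in expectation.
- Re-exposure adds nothing, so these people show no between-arm difference.

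Expected difference = (1 − q) × 3.75 + q × 0 = 3.75 × (1 − q). At unchanged SD and power, the required sample size is multiplied by 1/(1 − q)².

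| q | People among 170 | Difference | Sample size factor |
|---|---|---|---|
| 2% | 3.4 | 3.68 | 1.04 |
| 5% | 8.5 | 3.56 | 1.11 |
| 10% | 17 | 3.38 | 1.23 |
| 20% | 34 | 3.00 | 1.56 |

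If re-exposure still gave a fraction r of the full effect, the multiplier would be 1 − q(1 − r). With q = 10% and r = 0.5 it is 0.95, and 3.75 × 0.95 = 3.56. The table is therefore the pessimistic end for each q, provided that a second exposure does no harm.

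**The case against.** The strongest reply is that this is an argument from silence in a condensed article. No sentence permits re-screening, and the site may log people who fail. The article mentions a decision tree for combinations of criteria, and it lists registration as the first part of the therapy, so an ineligible user of the modules may well have an account. That stands against one tempting inference, that the site cannot recognise a returning person. The documents do not settle this. What they do show is a check built on allocation and an eligibility list without the needed line. Even a recognised earlier user is not excluded by any stated rule.

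Other stronger readings also fail:

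- **That explaining the rejection is the defect because it teaches people how to re-answer.** All the criteria are shown to everyone at consent, so the explanation adds little. Anyone could misreport at the first attempt. The Discussion already acknowledges reliance on self-report and says that under-age entry cannot be addressed further.
- **That re-answering defeats the cardiovascular and depression criteria.** This is a general limit of online self-report and not a consequence of offering the modules. People who re-answer at once have had no therapy, so the dilution argument does not cover them.
- **That the arms become unbalanced.** Re-entry comes before randomisation, so it does not itself unbalance them.

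The motive to return is also modest. A rejected person already has the active therapy. Coming back costs about 30 minutes of baseline assessment and risks allocation to psycho-education, and the 40 Euro is paid only for the 6-month follow-up. With 70% expected to quit before six weeks, many earlier users may have had little exposure. Someone first rejected for too little cocaine use would have to use more to qualify, which sits badly with a benefit already gained. All this argues for a small q, but not for leaving the route open.

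**Conclusion.** The point holds in limited form. As described, the plan can randomise people already exposed to the experimental therapy, against the stated aim of its own treatment exclusion. The consequences are previously treated people in both arms, a contaminated control condition and possibly a diluted contrast.

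The size cannot be derived from the documents: no re-entry rate is given, and no value of q is supported. The 1 − q factor is an illustration resting on the assumptions in the working. The conclusion also rests on reading other treatments as not including Snow Control, and on the duplicate check working as the article describes it. A reader might infer that every screening failure must be barred for good, but the documents do not call for that. The problem is prior exposure to the modules, not a second screening.

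**What to change.** Add one exclusion to Table 1: any previous use of Snow Control modules, including pilot participation. Check it at screening against existing Snow Control accounts and with one self-report item. People who failed screening but never opened a module can still be re-screened.

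If the sponsor prefers not to exclude earlier users, the minimum is to record prior Snow Control use at baseline and run a sensitivity analysis without those participants. Either way the information must be collected at entry, because use outside the study carries no assessments from which exposure could be reconstructed.

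The cost is one line in Table 1, one screening item and an account check. A few late-eligible applicants are lost, and a person with a new e-mail address and device can still evade the check.

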### Randomisation and Allocation

Once participants have completed their baseline assessment, they will be randomly brought to part 1 of either the intervention or the control tool, and this assignment will be automatically registered in the background database. This assignment will also be registered in their Internet browser as a cookie to avoid multiple registrations by one person. If a person returns to the Snow Control start page and attempts to register for a second time, she or he will be recognised by the background database and automatically be redirected to his or her allocation.

